## 2) Objectives\*

The goal of the proposed application is to evaluate in an effectiveness-implementation type I hybrid trial, an enhanced version of eHealth Familias Unidas for reducing depressive, anxious symptoms and suicide behavior in Hispanic youth. Using a randomized rollout design of 18 clinics, the study's aims are to:

**AIM 1:** Evaluate the effectiveness of eHealth Familias Unidas for Mental Health in preventing/reducing depressive, anxiety symptoms; suicide ideation and behavior; and drug misuse among those with poor family communication, elevated levels of depressive or anxiety symptoms, or a history of suicide ideation or behavior.

**H1:** eHealth Familias Unidas for Mental Health will be effective, relative to standard of care, in reducing these outcomes in Hispanic adolescents over time.

**AIM 2:** Determine whether intervention effects are partially mediated by family communication and externalizing behaviors, including drug misuse, and moderated by parental depression.

**H2:** Intervention effects on mental health outcomes will be partially mediated by improvements in family communication, externalizing behaviors (including drug misuse) and moderated by parental depression.

**Exploratory AIM 3:** Intervention impact on mental health and drug misuse as well as sustainment of the intervention in clinics will vary by quality of implementation at clinic and clinician levels.

## 3) Background\*

Mental health problems among adolescents, including depression, anxiety, suicidal thoughts and behaviors, as well as drug misuse are a significant public health concern. National surveillance research indicates that approximately 14% of adolescents ages 12 to 17 reported having a major depressive episode (MDE) within the past year. The death rate related to suicide, the second leading cause of death among adolescents in the United States (U.S.), increased 56% between 2007 and 2016, from 3.9% to 6.1%. Among Hispanic adolescents, approximately 15% reported having a past year MDE in 2018, a significant increase compared to 12.6% in 2015. Hispanic high school students reported higher rates of suicidal behaviors in the past year when compared to the general population of U.S. high school students, including having serious suicidal thoughts (16.7% vs. 15.8%) and suicide attempts (10.2% vs. 7.8%). In particular, 21% of Hispanic females report suicidal thoughts when compared to 18.4% of non-Hispanic white females. Further, mental health disorders developed during adolescence are shown to be associated with later negative health outcomes, including reoccurrence of depression and/or anxiety in adulthood, anxiety disorders, bipolar disorder, migraine headaches, poor self-rated health, low levels of social support, suicide attempts, alcohol/drug dependence, life dissatisfaction, and risky sexual behaviors.

Mental health disorders are comorbid with substance use behaviors among adolescents. Approximately 1.5% (358,000) of adolescents with an MDE also reported having a co-occurring substance use disorder (SUD). Substance use behaviors, including illicit drug, marijuana, opioid, risky alcohol, and cigarette use, were more prevalent among adolescents who reported a past year

MDE than their adolescent counterparts without a past year MDE. One study showed that 19.6% of Hispanic adolescents who reported suicide ideation also reported lifetime alcohol use, while 7.3% who reported suicide ideation did not report lifetime alcohol use. Similar disproportionate findings were found for Hispanic adolescents who reported lifetime and past 3-month illicit drug use, with 20.8% reporting suicide ideation and 12.5% reporting suicide attempts, compared to 8.4% and 5.2% of adolescents who did not report lifetime and past 3 month illicit drug use, respectively.

Evidence suggests family communication may work to reduce and/or prevent poor mental health and substance use outcomes in adolescents. For example, positive family relations were negatively associated with suicide risk among adolescents. Additionally, parent-adolescent communication has been shown to be negatively associated with both internalizing and externalizing behaviors in adolescents. Alternatively, negative family functioning, such as poor family communication, are shown to have adverse effects on adolescents' mental health. It is possible that for certain youth, family functioning protects against poor mental health outcomes indirectly by reducing externalizing behaviors, including substance use behaviors. In fact, research indicates that Hispanic adolescents who reported increased levels of parent-adolescent communication concurrently reported lower levels of externalizing behaviors (i.e., conduct problems). In another study, adolescent perceived parent communication was negatively correlated with both concurrent and subsequent past 30-day substance use behaviors. The role the family plays on mitigating adolescent mental health disorders may be particularly applicable to Hispanic families due to cultural values related to commitment, loyalty, and obligation felt towards the family system. Therefore, improving family communication should be an important focus when targeting the prevention of mental health and externalizing behaviors, including substance use, in Hispanic adolescents.

It is also important to take into consideration the effect of predisposing factors, such as parental depression, on adolescent internalizing behaviors. Reports show that 1 in 10 children in the U.S. have mothers who have experienced major depression in the past 12 months. Adolescents whose parents are depressed are at greater risk for reporting poor mental health outcomes as well. In a parent-child dyad study with children between the ages of 7 and 17, children of depressed parents reported higher levels of depression when compared to children of non-depressed parents (7.87 versus 4.82). Further, in a cognitive-behavioral preventative intervention targeted towards lowering adolescent depressive disorders, parental depression moderated intervention effects. Specifically, when compared to usual care, the intervention resulted in lower rates of depression but only for adolescents whose parents were not depressed.

Considering the co-morbidity between mental health disorders and drug use behaviors and the association of family communication with both, it is not surprising that family-based interventions developed to address drug abuse prevention have also shown crossover effects in reducing the prevalence of mental health symptoms among adolescents. One example besides Familias Unidas is the Family Check-Up (FCU) intervention, which was designed to reduce adolescent substance use and behavior problems through improvements in parenting and family functioning. Findings from the FCU intervention indicated that adolescents who engaged in the intervention reported lower levels of suicide risk in later adolescence and early adulthood. Another example of a family-based intervention is the Family Bereavement Program (FBP) designed for children who experienced the loss of a parent, with participants showing decreased suicidal risk 15 years after participating in the intervention. Our own synthesis of 19 adolescent preventive trials with a minority of these trials focused specifically on depression demonstrated a significant impact on depressive symptoms for two full years.

Very few interventions have been culturally tailored to the needs of Hispanic families. One of these interventions is Familias Unidas. Developed to address adolescent substance use and sexual risk behaviors by targeting family functioning, including family communication, Familias Unidas has also shown crossover effects lowering internalizing symptoms when compared to a control condition. The intervention's effect on reduced levels of internalizing symptoms was partially explained by a moderated mediation effect of parent-adolescent communication. That is, there were stronger mediated effects for adolescents with lower levels of baseline levels of parent-adolescent communication when compared to adolescents who reported higher levels of parent-adolescent communication at baseline. Additionally, among youth with externalizing symptoms, Familias Unidas had main effects on internalizing symptoms, one with moderated mediation on family communication and one through cascading effects by improving family communication, which in turn reduced externalizing behaviors, which in turn decreased internalizing symptoms. Finally, Familias Unidas significantly reduced suicidal attempts among adolescents with low levels of parent-adolescent communication. Specifically, the intervention, relative to prevention as usual, reduced the risk of suicidal attempts for adolescents who reported poor parent-adolescent communication (see preliminary findings).

Although intervention findings show promise, many of these interventions have not been assessed outside of a research setting, and thus, a knowledge gap exists on the successful integration of mental health evidence-based interventions into delivery systems such as health care systems. Primary care settings may afford an opportunity for successful implementation of evidence-based preventive interventions for three main reasons. First, primary care settings are visited often by adolescents. In 2017, approximately 74% of Hispanic adolescents under the age of 18 reported seeing a doctor or another health care professional in the last 6 months. Second, primary care doctors are seen as a trusted source of health information, such that parents often consult primary care providers with concerns they have regarding adolescent behaviors. Third, primary care settings may provide a solution for the underutilization of mental health care services by de-stigmatizing access to care. Hispanic populations are less likely to seek or use mental health services when compared to non-Hispanic white populations, and they rely on informal sources of support and primary care providers for help with mental health problems. For these reasons, existing research suggest that preventative mental health services can and should be provided in primary care settings in an effort to reduce the mental health disparities seen in Hispanic populations. Having primary care settings sustain interventions such as eHealth Familias Unidas after the research study ends is important. Such sustainment may vary as a function of clinic organization, organizational climate for evidence-based implementation, and clinic leadership (Aarons et al., 2015, 2017).

Despite the possible benefits of implementing evidence-based interventions in primary care settings, challenges exist. Commonly reported barriers by primary care personnel when implementing an intervention are time constraints and existing workloads. A possible solution to the limited time and resources afforded in primary care settings could be relying on internet-based (i.e., eHealth) interventions. According to the Pew Research Center, at least 80% of Hispanic adults access the internet via a mobile device such as a cellular phone or tablet). Further, trends indicate an increase among Hispanic adults in accessing the Internet via mobile devices, specifically from 76% in 2012 to 94% in 2015 (compared to 85% in non-Hispanic Whites), among internet users. Scientifically based and appropriately designed eHealth interventions offer the advantage of also reaching at-risk Hispanic adolescents while cutting the cost of relying on mental health providers. The feasibility and acceptability of an eHealth version of Familias Unidas has previously been examined, with high intervention engagement rates (84%) and positive participant feedback on the content of the intervention. Further,

eHealth Familias Unidas was found to be efficacious in reducing drug use, prescription drug use, and cigarettes use trajectories when compared to prevention as usual and improving overall family communication at 3 months post-baseline.

### **Preliminary studies.**

**Efficacy Study of Face-to-Face Familias Unidas in a School Setting.** [name] and colleagues evaluated the efficacy of Familias Unidas in preventing adolescent drug use, cigarette use, alcohol use, and unprotected sexual behavior, relative to (1) an HIV preventive intervention and (2) a cardiovascular preventive intervention. Participants ( $n = 266$ , mean age = 13.4,  $SD = .68$ ) were assessed at baseline, randomized, and reassessed at 6, 12, 24, and 36 months post baseline. Familias Unidas was efficacious, relative to the cardiovascular intervention in reducing past 90-day illicit drug use ( $z = 2.02$ ,  $p < .05$ ), efficacious relative to both the HIV intervention ( $z = 3.25$ ,  $p < .002$ ) and the cardiovascular intervention ( $z = 2.66$ ,  $p < .008$ ) in reducing past 90-day cigarette use, and in reducing unprotected sexual behavior at last sexual intercourse ( $\chi^2(1) = 3.87$ ,  $p < .05$ ). The effects of Familias Unidas were mediated by improvements in family communication.

**Replication efficacy study of Face-to-Face Familias Unidas in a School Setting.** [name] and colleagues evaluated the efficacy of Familias Unidas in reducing past-90 day illicit drug use and unprotected sexual behavior, relative to prevention as usual, among adjudicated Hispanic youth. 212 (mean age = 14.6,  $SD = 1.36$ ) juveniles and their primary caregivers were assessed at baseline and reassessed at 6 and 12 months post baseline. The results showed that Familias Unidas was efficacious, relative to prevention as usual, in improving family communication ( $b = .28$ ,  $p = 0.02$ ), increasing past 90-day condom use ( $b = 0.68$ ,  $OR = 1.97$ ,  $p = 0.015$ ), and in reducing past 90-day illicit drug use ( $b = -0.72$ ,  $p = 0.04$ ).

**Effectiveness Study of Face-to-Face Familias Unidas in a School Setting.** [name], [name] and colleagues evaluated the effectiveness of face-to-face Familias Unidas in reducing the frequency of drug use, alcohol use, and unprotected sexual behavior, relative to prevention as usual, among 746 Hispanic youth (mean age = 13.9,  $SD = 0.67$ ) recruited from 18 middle schools. School counselors were trained to deliver Familias Unidas. Participants were assessed at baseline and reassessed at 6, 18 and 30 months post baseline. The results showed that Familias Unidas was efficacious, relative to prevention as usual, in increasing family communication ( $b = -0.148$ ,  $p = 0.014$ ), reducing the frequency of past 90-day illicit drug use ( $b = 0.23$ ,  $p < 0.001$ ), and in reducing past 90-day unprotected sexual behavior ( $b = 0.093$ ,  $p = 0.008$ ).

**Efficacy Study of eHealth Familias Unidas in School Settings.** [name], [name] and colleagues evaluated the efficacy of an eHealth adaptation of Familias Unidas in reducing substance use and condomless sex among 230 Hispanic youth (13.6 years,  $SD = 0.7$ ). Youth were assessed at baseline, 3 and 12 months post baseline. Significant intervention effects were found across time for drug use ( $b = -1.16$ ,  $p < .01$ ), prescription drug use ( $b = -1.16$ ,  $p < .01$ ), and cigarette use ( $b = -1.05$ ,  $p < .01$ ). Effects were not found on condomless sex. In our past trials, significant effects on condomless sex began to emerge at 24-month post baseline.

**Pilot Study and Ongoing Study of eHealth Familias Unidas in Primary Care.** [name] and colleagues evaluated and established the feasibility and acceptability of delivering eHealth Familias Unidas in a universal sample of 33 Hispanic youth recruited from three primary care settings. This study led to the next trial.

**Relative Effectiveness of eHealth Familias Unidas in Primary Care to Prevent Drug Misuse and STIs.** This ongoing NIDA funded study uses a sample of 456 Hispanic youth recruited from 16 diverse primary care clinics. Only baseline, 6-month, and 12-month post-baseline data collection have been completed, and eHealth Familias Unidas has already shown an effect on

family functioning, a mechanism of action of the intervention. The percentage of sessions attended by the families randomized to the intervention exceeded 70%. Over 85% of families have currently been retained in the follow-ups.

*Crossover Effects on Internalizing Symptoms and Suicide Ideation.* Although eHealth Familias Unidas does not directly address internalizing symptoms, Familias Unidas has had crossover effects on both internalizing symptoms (consisting of depression and anxiety symptoms) and suicide ideation. One study led by [name] and colleagues found that, relative to control, Familias Unidas reduced internalizing symptoms among 242 delinquent 13- to 17-year-old youth. Improvements in family communication mediated the intervention's effects on internalizing symptoms for youth whose families had poor communication. A second study of 721 Hispanic youth (14.0 years; SD=1.14) found reductions in internalizing symptoms for youth with low family communication through intervention-mediated improvements in communication across three pooled Familias Unidas trials. A third study among youth with externalizing behaviors documented cascading effects on internalizing symptoms through the intervention's impact on improving family communication, followed by subsequent reductions in externalizing behaviors, and ultimately reduced internalizing symptoms. In terms of suicide, a fourth study of a single trial showed that at baseline 9.2% of adolescents had recent suicide thoughts and 5.7% a suicide attempt, with 12.2% reporting thoughts and 8.6% reporting attempts among the 18.8% of those reporting poor family communication. This study found that Familias Unidas significantly reduced suicide attempts compared to control (OR = .53,  $p < .05$ ) for youth reporting poor family communication.

It is important to note that the effects sizes between eHealth Familias Unidas and Control vs Face-to-Face Familias Unidas and Control in prior studies have not been significantly different across the various outcomes (except for smoking which is not an outcome in this study). Additionally, participants in eHealth Familias Unidas had greater attendance than those in the face-to-face version of the intervention, and attendance in the intervention is related to improved study outcomes.

Although the original Familias Unidas and eHealth Familias Unidas interventions do not specifically target youth internalizing symptoms, studies have demonstrated cross-over effects on mental health, reducing youth internalizing symptoms and suicide attempts. These crossover effects may be explained by common underlying parent and family risk and protective factors associated with adolescent depressive, anxiety, and suicide symptoms. Common risk factors include family conflict and parental rejection, while common protective factors include positive family communication and parental warmth. Positive parenting and family functioning are also protective for adolescent externalizing symptoms and drug use, which are risk factors for later internalizing symptoms. It is therefore not surprising that Familias Unidas has been found to reduce multiple youth mental health and behavioral outcomes through intervention-mediated improvements in family factors, such as family communication. Other preventive interventions targeting parent and family factors have documented improvements in internalizing symptoms through their impact on these common intervention mechanisms, such as by reducing family conflict or improving parent-child. Additionally, poor mental health in parents can interfere with the effects of programs that aim to prevent adolescent mental health problems. As a result, addressing parent mental health is an important objective in programs to promote adolescent mental well-being.

#### 4) **Inclusion and Exclusion Criteria\***

Families will be screened based on the following inclusion criteria:

- (a) Female and male adolescents, who self-identify as Hispanic (or Latino(a))

- (b) Adolescent between the ages of 12 – 16 years
- (c) Adolescent living with an adult primary caregiver who is willing to participate
- (d) Families must have broadband internet access on a device, including (but not limited to) a smartphone, iPad, tablet, computer at their home or other location (e.g., school, library, etc.)
- (e) Families screening positive on poor family communication (a score of less than 75 on the communication measure; see measures) or youth reporting elevated depressive or anxiety symptom scores or a history of suicide behavior (ideation or attempts)

Exclusion criteria: Families reporting plans to move out of the South Florida area during the study period.

## 5) Procedures Involved\*

**Design.** To evaluate eHealth Familias Unidas Mental Health in an effectiveness-implementation hybrid Type 1 trial, this study will use a rollout design, which is an extension of a Stepped Wedge design. We will balance, and then randomize all 18 sites into five cohorts of 4 or 3 clinics to when they would end their control phase, when they would begin receiving eHealth Familias Unidas Mental Health, and when they would start the sustainability period where UM staff would no longer provide formal support (i.e., clinical supervision) to the clinic to deliver eHealth Familias Unidas Mental Health. This design is an extension of a Stepped Wedge design since it has three conditions (as shown in the figure) and provides both within and between clinic comparisons of effectiveness over time. Youth and parents will be assessed at baseline, 3-, 6-, and 18-months post-baseline. We will collect electronic health record data (e.g., exposure to an antidepressant) for participants during their control phase.

**Participants.** The sample will consist of 468 Hispanic female and male adolescents and their primary caregivers recruited from one of 18 primary care clinics, who meet the inclusion/exclusion criteria below. We will include a mix of naive and previously involved clinics in the proposed study. Because we did not attempt to institutionalize eHealth Familias Unidas in earlier involved clinics, we do not anticipate much difference in effect, but we will test for this.

A document to assess for the inclusion/exclusion criteria will be included as part of the patient check-in process. We will screen parents and adolescents separately to verify the inclusion and exclusion criteria. Adolescents will be asked questions regarding their mental health (reporting elevated depressive or anxiety symptom scores or a history of suicide behavior) and parents will be asked questions related to communication with their adolescent.

**Recruitment.** Participants will be recruited from 18 primary care clinics.

[figure not shown]

The sites are heterogeneous and consist of federally qualified health centers, academic primary care clinics located within the University of Miami's Health District, and private community clinics. Collectively, these sites jointly serve over 10,000 Hispanic between the ages of 12 -16 per year. Therefore, we do not anticipate any challenges in recruiting 468 youth over the 18-month recruitment period.

Families who meet the study's inclusion/exclusion criteria will automatically be connected via protected videoconference software to the research team via an iPad. The team member will explain the study to eligible participants and complete the e-consent process. Families who enroll will then be sent a link to complete the assessment battery on the iPad while they wait to see the physician. The clinic staff member will thank the study participant for enrolling in the study and will make a hand off to the physician. If the family is unable to complete the survey at the clinic, a link will be sent to them so that the survey can be completed at their convenience. Families will also have the option to complete the follow-up surveys via a link that is emailed to them.

As an additional form of recruitment, clinic doctors will also provide families with a note where they recommend the program. If the family is interested in participating, they will provide their contact information and a research team member will call them to explain the study.

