mechanism by which to ensure secure access and confidentiality for participants. Each participant will be assigned a unique log-in name and password, which will provide them access to the eHealth Familias Unidas Mental Health session. The log-in procedure will also facilitate the close monitoring of participants, particularly as it relates to session participation rates. Specifically, the log-in procedure will be utilized to record who (i.e., which participant), when (i.e., day/time), how long (e.g., time of session attendance), and for what purpose (e.g., which session) the intervention website was accessed.

Our information technology team employs the latest technology to ensure security and confidentiality of participants, including but not limited to data error checking through forms, filtering output, and the use of encryption. Server Port Hardening will be implemented to keep the web server safe from intrusion. Additionally, a Secure Socket Layer Encryption certificate will be issued to help prevent Internet fraud. The implementation of SSLs (i.e., cryptographic protocols) aims to enhance security over the Internet. IT will conduct stringent testing of web applications prior to the implementation of eHealth Familias Unidas Mental Health to prevent any exploits from occurring and to ensure the confidentiality of participants.

-All participants will not receive the intervention. Participants will receive the intervention depending on when the clinics offer the program, which is based on the study's randomization. After the intervention is complete, assessors will call the families to return to complete follow up assessments. The follow up assessments will occur online through links emailed via REDCap.

The follow up assessments collect the same data as the baseline assessment. All measures will be self-report. We will ask participants to give us the names and telephone numbers of three people who will always know how to reach them, in case we lose contact. We will never share anything participants tell us with these people.

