## **13) Recruitment Methods**

Screening will take place in pediatric care clinics. Screening will be included into the patient check-in process. Parents and adolescents will complete the screening separately on tablets provided by the research team. REDCap programming will be used to determine whether the participant meets the screening criteria. Families who meet study inclusion/exclusion criteria will automatically be connected via protected videoconference software to the on-call study team via iPad to complete the e-consent process. If a videoconference call is not possible, arrangements will be made at a convenient time for the participant. The team member will explain the study to eligible participants and complete the e-consent process. Families who enroll will then be sent a link to complete the assessment battery via iPad while they wait for the physician. The clinic staff member will thank the study participant for enrolling in the study and will make a hand off to the physician. We will screen and enroll youth with poor family communication or elevated depressive or anxious symptoms, as well as those with a history of

suicide ideation or attempts (see inclusion criteria).

Participants will be assessed at baseline and 3-, 6-, and 18- months post-baseline. We have budgeted the following amounts for participant parent incentives: T1=\$40, T2=\$45, T3 = \$50 and T4= \$55. Adolescents will receive two movie tickets and \$20 for each completed assessment. The participant incentive cost will reimburse study participants for time and effort to participate in the baseline and each of the follow-up assessment activities.

As an additional form of recruitment, clinic doctors will also provide families with a note where they recommend the program. If the family is interested in participating, they will provide their contact information and a research team member will call them to explain the study. We will also distribute flyers in the clinics to recruit participants. These flyers will contain a QR code that can be scanned by potentially interested participants. Once scanned, participants will be able to provide their contact information so that they can be reached and given more information about the study.

Additionally, we will do the following:

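### Youth are recruited after clinics are randomized, and one route is a doctor's note recommending a program only intervention-phase families receive, so recruitment, and with it regression to the mean, could differ by phase

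*Protocol*

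**What the plan says.** **Randomization and enrolment.** Protocol Section 5, Design: "We will balance, and then randomize all 18 sites into five cohorts of 4 or 3 clinics". Section 7, Aim 1, adds that every clinic enrols youth in both its control and its intervention period. What a family gets follows the clinic's phase: "Participants will receive the intervention depending on when the clinics offer the program, which is based on the study's randomization" (Section 5, Intervention conditions). No masking of recruiters is described.

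**Recruitment routes.** The main route is screening at check-in: "A document to assess for the inclusion/exclusion criteria will be included as part of the patient check-in process" (Section 5, Participants). Section 5, Recruitment, adds a second route: "clinic doctors will also provide families with a note where they recommend the program". Section 13 repeats it in the same terms. An interested family leaves contact details and is then called to hear about the study. Section 13 also lists flyers with a QR code, appointment lists at the university's own clinics, and a registry mailing that names the intervention project. No wording specific to phase is given for any of these.

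**Entry and baseline.** Section 4(e) lets a family in by any of three routes. The first concerns communication: "Families screening positive on poor family communication (a score of less than 75 on the communication measure; see measures". The second and third are symptoms and suicide history, and need no low communication score: "youth reporting elevated depressive or anxiety symptom scores or a history of suicide behavior (ideation or attempts". The battery follows consent: "Families who enroll will then be sent a link to complete the assessment battery on the iPad while they wait to see the physician" (Section 5, Recruitment).

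**Analysis.** Section 7, Aim 1, fits growth models to baseline, 3, 6 and 18 months, treats clinic as a blocking factor, and tests the difference between conditions in average slope.

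**The concern.** Randomizing the date on which a clinic crosses over does not balance who is recruited before and after that date. Balance then depends on recruiting in the same way in both phases, and the note works against this. It endorses the program, which a control-phase family will not get. Either it tells control-phase families something inaccurate, or it will tend to be used more once there is a program to offer. The protocol does not say which.

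This matters for the planned test because of where baseline sits. A youth who qualifies on a momentarily raised symptom score tends to have a raised baseline too when the battery follows at the same visit, and then improves on average without any treatment. If one phase holds more such youth, its mean slope is steeper for that reason alone. A stable difference in severity would not by itself bias a slope contrast; the transient part would. Blocking on clinic compares phases within a clinic, and that is where the recruitment difference would arise.

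**Working it through.** **1. The plan's own figure.** Section 7, Power Analyses, gives 87% power for an effect size of 0.5 at a type I error of 0.05. With 468 youth split 234 and 234 and no clustering, a two-sided test has 99.97% power. The stated 87% corresponds to a standard error of 0.5 / (1.960 + 1.126) = 0.162, an effective 2 / 0.162² ≈ 76 per arm, and a design effect of 234 / 76.2 ≈ 3.07. The protocol text at hand gives no intraclass correlation, split between conditions or dropout allowance, so the 87% can be neither reproduced nor faulted. It is not contested here.

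**2. Formula for the bias.** Let μ be the mean symptom score of youth entering by symptoms, in SD above the other entrants; ρ the correlation between baseline and follow-up; and Δ the difference between phases in the share entering by symptoms. The spurious difference in change from baseline is

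b = (1 − ρ) × μ × Δ.

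**3. Inputs, all assumed; none is in the protocol.**
- Symptom-positive means the top 15% to 25% of a normal distribution: μ = 1.554 or 1.271.
- ρ = 0.5 to 0.8.
- Δ = 5 to 30 percentage points.

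**4. Results.**

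| Case | Calculation | b (SD) |
|---|---|---|
| No difference by phase | Δ = 0 | 0 |
| Lowest | 0.2 × 1.271 × 0.05 | 0.013 |
| Middle, low | 0.3 × 1.554 × 0.10 | 0.047 |
| Middle, high | 0.4 × 1.554 × 0.20 | 0.124 |
| Highest | 0.5 × 1.554 × 0.30 | 0.233 |

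The sign follows the sign of Δ. The formula treats the screening score as if it were the baseline score and treats the whole excess as able to regress. Both make b larger than it would otherwise be.

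**5. From early change to slope.** Regression to the mean acts mainly between baseline and the first follow-up. Suppose it is a step of size b at 3 months that then stays flat, with equal weights and untransformed time. The visits 0, 3, 6 and 18 have mean 6.75, deviations −6.75, −3.75, −0.75 and 11.25, and sum of squares 186.75. The fitted 18-month change is b × 18 × (−3.75 − 0.75 + 11.25) / 186.75 = b × 18 × 6.75 / 186.75 = 0.65b. The middle cases become 0.03 to 0.08 SD and the highest 0.15 SD. Section 7 also plans to examine transformations of the time axis, which would change this factor.

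**The case against.** Much can be said on the other side, and most of it limits the size of the point rather than removing it.

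- **Entry is not simply a high baseline score.** A reader might infer that the baseline symptom score is itself the criterion for entry. It is not: eligibility is decided on a separate screener, and poor family communication alone is enough. Regression to the mean on symptoms therefore concerns mainly those who enter by symptoms. Having both steps at one visit leaves that subgroup little protection.
- **The protocol does not restrict the note.** A reader might infer that doctors use it only after crossover, or hand it to the youth who worry them most. Neither is stated. The note's text is not shown, the follow-up call explains the study, and *program* may be loose wording, although Section 5 uses the same word for the intervention. The note could equally draw motivated families with milder symptoms.
- **Timing for note families is open.** The same-visit sequence is described for check-in. When a family recruited by note is screened and assessed is not stated.
- **Safeguards exist.** Criteria are the same in both phases, and at check-in REDCap programming decides eligibility. Check-in screening would find many of the youth a doctor might refer, so the note's share may be small.
- **Condition known at baseline.** The battery follows the explanation of the study, so a reader might infer that it is answered with the condition known. The protocol does not say what families are told about the clinic's phase by then.

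What stands is that nothing in the protocol makes recruitment the same in both phases, and that one stated route promotes something available in only one of them.

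**Conclusion.** The point holds as a possible bias of unknown direction and size. The protocol establishes its elements: enrolment after cluster randomization, a note recommending what only one phase delivers, symptom elevation as one entry route, and baseline inside the slope contrast. It does not establish that recruitment will in fact differ by phase; if it does not, the bias is zero. The range of 0.01 to 0.23 SD in early change rests entirely on the assumed share difference, symptom cut and correlation.

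It is tempting to express that range as a fraction of the planned effect size of 0.5, or to convert it to a type I error through the standard error of 0.162. The documents do not support this. The 0.5 refers to a slope over 18 months, its scaling is not stated, and an early drop in score does not pass into that slope one for one. The point is worth acting on because the remedy is nearly free, not because a large bias has been shown.

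**What to change.** 1. In Section 5 (Recruitment) and Section 13, replace the note with a condition-neutral invitation to take part in the study, used identically in control and intervention phases. Align the flyer and registry wording with it.
2. Record for every family the recruitment route (check-in, doctor's note, flyer, appointment list, registry) and the criterion or criteria on which it qualified.
3. Compare route and screening severity between phases.
4. Repeat the main analysis in families recruited through universal check-in screening only. The detail can sit in the statistical analysis plan, but the route must be captured at recruitment because it cannot be reliably recovered later.

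Adjusting for route as a covariate is not a substitute: if route tracks phase, it cannot separate route from condition. The check-in-only analysis has its own limit, since willingness to consent could still differ by phase. Withholding the clinic's phase until after baseline is not proposed, because it would alter the consent conversation and is not clearly cheap.

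**Cost.** New wording, two REDCap fields and one sensitivity analysis. A neutral note may recruit slightly fewer families. Section 5 reports over 10,000 Hispanic youth of eligible age per year, or about 15,000 over the 18-month recruitment period, for 468 places (468 / 15,000 ≈ 3%). Not all of these will meet criterion (e), but a small loss looks affordable.
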